### Expected outcome

2.5

The expected outcome of this study is an increase in depression literacy among secondary school students in the intervention group.

### Ethical consideration

2.6

This study protocol was approved by a Faculty of Medicine Research Ethics Committee at Jazan University. Consent will be received from the managers of the selected schools. Before participation, students will be informed that the collected information will be kept anonymous and that participation is absolutely voluntary. The participants will be assured that they could withdraw from the study at any time. Informed consent will be sought from the eligible participants following a full disclosure regarding the study. Proxy consent for the children will be obtained from their guardians and from each child who is eligible to participate in the study before randomization.

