### Trail design, study area, and target population

2.1

A cluster-randomized trial design will be employed for this study. The study will be conducted in Jazan City, the capital of Jazan region, lies in the south-western part of the Kingdom of Saudi Arabia. There are 13 governmental secondary schools (6 for boys and 7 for girls) in Jazan City. Inclusion criteria involves; students who are enrolled in one of the selected schools; participants in the age group of 10 to 19 years, and students who agreed to participate in the study (consent will be obtained from students, and proxy consent will be obtained from guardians). There were no exclusion criteria for participation in this study.

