### Sampling size and design

2.2

The sample size calculation will be conducted to determine the number of participants required. Based on the study's design, an intracluster correlation coefficient (ICC) of 0.02 will be used in sample size calculation based on similar studies,^[15,16]^ and an effect size of 0.5 will be used to detect the medium effect of the intervention based on similar studies by Perry et al^[15]^ and Gulliver et al,^[13]^ which used the same design and assessment tool (the depression literacy questionnaire [D-Lit]). Other parameters for estimating sample size include a 95% confidence interval and an Alpha coefficient of 5%. Accounting for a 10% non-response and/or drop-out rate, the total required sample size will be 360 students, 180 of whom will be recruited for the intervention group and 180 for the control group. The unadjusted sample size calculation will be conducted using the G∗Power program (version 3.1.9.1; Heinrich Heine Universität, Düsseldorf, Germany)^[17]^, then adjusted for the cluster design effect according to the methods outlined in Campbell et al.^[18]^

For sampling procedures in stage one 13 secondary schools in Jazan city will be stratified according to sex (6 schools for boys and 7 schools for girls). In stage two, 1 school from each stratum will be selected at randomly for the control group, and another one from each stratum will be selected at randomly for the intervention group using the closed envelope technique. Finally, in sage three and based on the calculated sample size of 360, random sampling technique will be used to recruit 180 students from the control schools (1 boy's school and 1 girl's school) and 180 students from the intervention schools (1 boy's school and 1 girl's school) (see Figure 1, Supplemental Content which illustrates the sampling procedures).

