##### Lectures

2.3.2.1

There will be 2 lectures of around 30 minutes; 1 lecture will be held each weak. Thirty students will attend each lecture. Therefore, each intervention school (90 students) will be divided into 3 groups (30 students in each); the first lecture will cover recognition, risk factors, and causes of depression. The second lecture will cover depression treatments—including antidepressants and cognitive behavioral therapy—as well as the professional help available and appropriate ways to seek help.

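### Schools are drawn straight into an arm and consent is taken from managers of the selected schools, so a manager's refusal can follow allocation and may depend on the arm

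*Protocol article*

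**What the plan says.** Section 2.1 gives the pool: "There are 13 governmental secondary schools (6 for boys and 7 for girls) in Jazan City". Section 2.2 stratifies these schools by sex. In its second stage "1 school from each stratum will be selected at randomly for the control group". The intervention schools are drawn in the same step, where "another one from each stratum will be selected at randomly for the intervention group using the closed envelope technique". No earlier step picks schools without giving them an arm. Students come in the third stage, when "random sampling technique will be used to recruit 180 students from the control schools (1 boy's school and 1 girl's school"), with 180 more from the intervention schools.

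On school-level agreement, section 2.6 says only: "Consent will be received from the managers of the selected schools". It does not say when managers are approached or what they are told. The same section says that consent is obtained from guardians and "from each child who is eligible to participate in the study before randomization". That sentence concerns guardians and children, not managers.

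Section 2.3.2 and its subsections describe what an intervention school must provide: a teacher to be trained and to deliver the programme, equipped classrooms, two weekly lectures for each of three groups with discussions, a video, brochures and posters. Control schools take part only in the questionnaires of sections 2.3.1 and 2.3.3.

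**The concern.** In section 2.2 a school is selected only by being drawn into an arm. If consent is then sought from managers of selected schools, the natural order is draw, allocate, ask. At that point the request differs between arms: one manager is asked to host a two-week programme, the other to allow questionnaires. If managers know which they are being asked for, willingness to host can decide which schools end up in the intervention arm and has no such role in the control arm.

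Randomising schools protects the comparison only if the schools analysed are the ones that were randomised. With many clusters, one refusal does little harm. With two schools per arm, each the arm's only school of its sex, one refusal either empties a sex stratum in one arm or brings in a substitute after allocation. A manager who welcomes a mental-health programme may run a school that differs in depression literacy, stigma or receptiveness to teaching.

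**Working it through.** **1. The plan's own figure.** Inputs from section 2.2: effect size 0.5 SD, alpha 0.05, ICC 0.02, 10% loss, 180 students per arm. Power and sidedness are not stated; I assume 80% and two-sided.

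- Unadjusted n per arm = 2 × (1.96 + 0.84)² / 0.5² ≈ 63 (64 by t test).
- Design effect with 81 completers per school (90 × 0.9) = 1 + 80 × 0.02 = 2.60.
- n per arm = 63 × 2.60 / 0.9 = 182 (185 with the t-test figure), within 3% of 180.

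The total of 360 is thus reproduced approximately under these assumptions. It is not in dispute here.

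**2. What one school represents.** 360 / 4 = 90 students per school. Section 2.3.2.1 confirms this for the intervention arm: "each intervention school (90 students) will be divided into 3 groups (30 students in each"). An equal split in the control arm is assumed. So 90 / 180 = 50% of an arm and 100% of that sex in it.

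**3. If a refusing school is not replaced.** Two-sided 0.05, normal approximation, with SE = √[DE × (1/n₁ + 1/n₂)] and power = Φ(0.5/SE − 1.96). DE is 1 + 89 × 0.02 = 2.78 with all 90 students per school, and 2.60 with 81.

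| Comparison | DE | SE | Power |
|---|---|---|---|
| 180 v 180 | 2.78 | 0.176 | 81% |
| 90 v 180 | 2.78 | 0.215 | 64% |
| 162 v 162 (10% loss) | 2.60 | 0.179 | 80% |
| 81 v 162 (10% loss) | 2.60 | 0.219 | 62.5% |

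These figures take the ICC at face value and make no allowance for having only three or four schools. They serve to show the size of the drop.

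**4. If it is replaced.** Numbers and nominal power are kept. The cost moves to validity: one of the arm's two schools was chosen after allocation. The design-effect adjustment in section 2.4 enlarges the variance; it does not correct for which schools agreed.

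**5. How often this might happen.** The documents give no refusal rate, so p below is an assumption, with managers deciding independently.

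| Assumed p | At least one of 2 intervention schools, 1 − (1 − p)² | At least one of all 4 schools, 1 − (1 − p)⁴ |
|---|---|---|
| 5% | 10% | 19% |
| 10% | 19% | 34% |
| 20% | 36% | 59% |

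**6. The two sections side by side.** Section 2.2: schools enter arms in stage two, students are sampled in stage three. Section 2.6: guardians and children consent before randomisation. If randomisation means the school draw, that consent would have to precede the sampling of the students concerned. The only timing statement on consent therefore does not fit the sampling sequence, and it does not mention managers.

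**The case against.** The strongest reply is that the order is inferred. Section 2.6 gives no timetable for managers, and the word describing the schools may only identify whose consent is held. The one consent whose timing is given is placed before randomisation. When gatekeepers are approached is also a detail that a journal article often leaves to the full protocol. Part of this stands: the sequence is the plain reading of two sections taken together, not a stated schedule, and the absence of a replacement rule is not counted as a fault. What remains is that the article does fix how schools are selected, directly into an arm, and ties manager consent to schools so selected. The timing statement for guardians and children does not cover managers and itself conflicts with section 2.2.

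A reader might also infer that refusals will be caused by the allocation. The documents do not support that: they do not say that managers know the arm when asked, and a refusal could have unrelated reasons. The unequal burden supplies a possible motive only.

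A reader might further infer that any resulting difference between schools could never be told apart from the intervention effect. That too goes beyond the text. Section 2.3.1 measures D-Lit, DSS and SSDS in both arms before the intervention, and section 2.4 tests baseline differences and changes over time. A baseline imbalance in these scores would be partly visible. Testing for it does not remove it, and differences in receptiveness that the scales do not capture would stay hidden.

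Finally, approaching all 13 managers would be more than the problem requires. That is right, and the fix does not depend on it.

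**Conclusion.** The point holds as a weakness in the stated sequence. Followed as written, sections 2.2 and 2.6 let a manager's decision come after allocation, in a trial where one school is half an arm and the whole of one sex in it. The consequence of one refusal is either a drop in power from about 81% to 64% (80% to 62.5% after 10% loss) or an arm half made up of a school chosen after allocation. The power figures rest on the plan's ICC of 0.02 and effect of 0.5, with an assumed two-sided test.

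The documents do not show that any manager will refuse, that managers know the arm, or that the comparison is biased; the refusal probabilities are illustrations on assumed rates. The point should be corrected because the safeguard costs almost nothing, not because harm has been shown. If managers are in fact approached before the draw, one sentence saying so settles this part, and the conflict over guardian and child consent would still need to be reconciled.

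**What to change.** Separate selection from allocation in section 2.2:

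1. Within each sex stratum, put the schools in random order and take the first two.
2. Obtain each manager's agreement to take part in either arm. Replace a refusing school at this stage with the next in the random order.
3. Only when both schools in the stratum have agreed, open the envelope that assigns one to control and the other to intervention.

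Asking all 13 managers first and drawing from those who agree is an acceptable alternative.

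State the same order in section 2.6 and reconcile it with the statement on guardian and child consent. If student sampling and consent can be completed before the envelope is opened, that statement becomes true; if not, it should be reworded to match the actual order. Report how many schools were approached and how many agreed.

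Cost: the minimum stays at four managers, with one more contact per refusal, or 13 − 4 = 9 more under the alternative. The sample size stays at 4 × 90 = 360. The downside is that results apply to schools willing to accept either arm.

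### Consent is promised before randomization, but the sampling stages allocate schools before eligible students can be identified, so consent and baseline follow allocation with nothing said to conceal the arm

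*Protocol article*

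**What the plan says.** Section 2.6 (Ethical consideration) places consent ahead of randomization: it comes from guardians and "from each child who is eligible to participate in the study before randomization". The same section states that "Informed consent will be sought from the eligible participants following a full disclosure regarding the study", and for the schools that "Consent will be received from the managers of the selected schools".

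Section 2.2 (Sampling size and design) describes three ordered stages. The 13 schools are first stratified by sex. In stage two "1 school from each stratum will be selected at randomly for the control group". The same stage also draws the intervention schools, one per sex, with closed envelopes. In the last stage "random sampling technique will be used to recruit 180 students from the control schools", with the same number from the intervention schools.

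Section 2.1 lists among its inclusion criteria "students who are enrolled in one of the selected schools" and "students who agreed to participate in the study". Section 2.3.1 (Phase one) describes the baseline questionnaires as given to the control and intervention groups.

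**The concern.** In a cluster trial, the school can be allocated fairly and the comparison still be unbalanced, because the students who agree may differ between arms. This can happen when agreement is sought after the arm is fixed and can be learned. It matters here because participation is voluntary and agreement is an inclusion criterion. The outcomes are self-reported depression literacy and stigma, and willingness to join a school programme on depression is plausibly related to both. Baseline answers given by students who know their school's arm are exposed to the same problem.

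The analysis in section 2.4 would not repair it. It names t tests of group means and of changes over time, a baseline comparison and a design-effect adjustment. A design effect widens the standard error and leaves the estimate where it is. With one school per sex in each arm, a difference caused by unequal refusal also could not be separated from an ordinary difference between schools.

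**Working it through.** No figure in the plan bears on this point; the sample size of 360 does not enter. The check is on the order of events.

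1. **When a student becomes eligible.** Section 2.1 requires enrolment in a selected school, so eligibility cannot be established until schools are selected.
2. **When a school is selected.** Section 2.2, stage two, draws one school per stratum for control and another for intervention. The document has no stage in which a school is selected but not yet allocated.
3. **When students are recruited.** This is the final stage of section 2.2, and the schools are already named there by arm.
4. **What follows from 1 to 3.** Eligible students can first be identified after their school's arm is fixed. Consent of each eligible child before school randomization, as in section 2.6, has no place in this sequence.
5. **Could consent be sought in all 13 schools before the draw?** Sections 2.1 and 2.6 argue against it: eligibility is limited to selected schools, and school-level consent comes only from the managers of selected schools.
6. **Could randomization in section 2.6 mean the random sampling of students in stage three?** The conflict of wording would then disappear, but consent would still follow the allocation of schools, so the risk would remain.
7. **Is the arm concealed at consent or baseline?** The document does not say so. It mentions closed envelopes for the draw, but not who learns the result or when.

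A second check is whether separating selection from allocation would alter the randomization. Assume equal-probability draws.

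- Boys, 6 schools. Present scheme: a given control and intervention pair has probability 1/6 × 1/5 = 1/30. Drawing two schools unlabelled and then assigning arms: 1/15 × 1/2 = 1/30.
- Girls, 7 schools. Present scheme: 1/7 × 1/6 = 1/42. Separated: 1/21 × 1/2 = 1/42.

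The chance of every pairing is unchanged; only the time at which the arm becomes fixed moves.

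**The case against.** The strongest reply has four parts.

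**Fixed is not the same as known.** A reader might infer that students and guardians decide, and students answer the baseline questionnaires, knowing their arm. The documents do not support that. They show that the arm is fixed by then, not that anyone has been told. A condensed article may also leave concealment to a fuller protocol, so silence on it alone would be no finding. This stands, and the point is therefore put as a risk. The stated order and the stated promise still conflict.

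**Randomization may mean student sampling.** At the level of the individual child, the only random step is stage three. This reading is possible, so the wording conflict is not beyond dispute. It does not move consent ahead of school allocation.

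**Safeguards exist.** Students are drawn at random rather than volunteering, so selection can act only through refusal. All three scales are measured before the intervention in both arms, baseline scores are compared, and change within groups is analysed. These limit the risk and may reveal it. They do not prevent unequal refusal, and change scores carry forward any distortion in the baseline answers.

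**No size can be given.** A reader might assume a shift of 0.1 to 0.2 SD and call it 20% to 40% of the planned effect (0.1/0.5 and 0.2/0.5). The document supplies no such shift. Its only related figure is 10% for non-response and drop-out combined. Suppose all of that were refusal, in one arm only, with normal scores. If exactly the most extreme 10% refused, the mean would move by φ(1.2816)/0.9 = 0.195 SD. So 0.2 SD is about the worst case under that assumption, and 0.1 SD would need a correlation of about 0.1/0.195 = 0.51 between refusal and outcome. Correlations of 0.2 to 0.3 give about 0.04 to 0.06 SD, or 8% to 12% of the 0.5 SD effect. Similar refusal in both arms would cancel; higher refusal, or opposite selection in the two arms, would give more. These figures illustrate the range and are not estimates.

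It would also be wrong to infer that teachers decide on participation, or that teachers or guardians complete questionnaires. Section 2.3.2 gives teachers a delivery role, and guardians only consent.

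**Conclusion.** The point holds as an inconsistency with a consequence. Taking randomization to mean the allocation of schools, sections 2.2 and 2.6 cannot both be carried out. On either reading of the word, consent and baseline follow allocation, and nothing in the document conceals the arm. The result is a risk of refusal and baseline responses differing by arm. That this bias will occur is not shown, and its size cannot be derived from the document. The conclusion rests on the stages in section 2.2 being carried out in the order written. The change is worth making because it is cheap before recruitment and cannot be made afterwards.

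**What to change.** Split stage two of section 2.2:

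- Draw two schools from each sex stratum without an arm label.
- In all four schools, draw the random student sample, obtain student and guardian consent, and complete the Phase one questionnaires.
- Only then open the closed envelopes that assign the two schools in each stratum to control and intervention.

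Align sections 2.2, 2.3.1 and 2.6 to this order. Sample size, number of schools, instruments and programme stay as they are. The cost is a delay: allocation, and the training of teachers in the intervention schools, must wait until consent and baseline are complete for all 360 students in the four schools.

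If the order cannot change, correct the statement on consent timing in section 2.6, and keep students, guardians and those recruiting unaware of the school's arm until baseline is complete. This is the weaker remedy, because it depends on the concealment holding within each school.

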### Protocol amendment and data dissemination

2.7

The results of Trial will be disseminated through scientific conference and seminars presentations and by publication in peer reviewed scientific journals. Modifications of the trial protocol will only be done in consultation with investigators. Substantial amendments of the protocol require the approval of the Ethics Committee.

## Discussion

3

Many studies have concluded that educational intervention centered around the facts about depression and destigmatization improves knowledge and may decrease stigma.^[29]^

Accumulated evidences suggested the importance of educating adolescents about depression, because this is the peak period for the onset of mental disorders, with half of the people who will suffer from a mental disorder having their first episode before 18 years of age.^[30]^ There is some evidence that receiving mental health information at school can result in reductions in stigmatizing attitudes.^[22,31]^ Further research, intervention and activism are needed in the field of mental health in Arab countries to improve the awareness of mental health problems.^[32]^

Despite the need for such program especially in our region, where there is more stigma attitude, no studies or few have been conducted shed the light on this important area of research.

The proposed research will assist in improving mental health literacy on depression following an educational intervention program. Strengths include that the program will be conducted by students’ teachers at their schools, mimicking the natural sitting, which will lead to outcomes that can be generalized. If positive trends result from the present trial, they will support the development of further longitudinal work on a larger scale, for combating the stigma associated with depression, which is urgently needed in this field.

Limitations include the fact that the intervention will be conducted by 2 independent teachers, 1 from each school, but effect of this will be minimized by giving a short training for both teachers so that they would deliver identical programs.
